### Sample size calculation

To calculate the required sample size, the primary outcome is taken into account. According to a previous retrospective study (26), the 3-year disease-free survival (DFS) is 47.6% for RTA and 32% for TH. Then, we calculated 212 patients (106 in the RTA group and 106 in the TH group) need to be enrolled in this trial using a one-sided two-sample t-test. The conventional type I error is 5%, the statistical power is 90%, and the dropout rate is 15%. Prior to participating in the trial, every center should report the number of patients likely to be recruited with reference to the number of patients admitted in recent years for Siewert II AEG.

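### The planned 212 patients give about 70% power on the protocol's own inputs, not the stated 90%

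*Protocol article*

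**What the plan says.** All the relevant figures are in one paragraph of the protocol article, Sample size calculation. It takes the effect from an earlier retrospective study: "the 3-year disease-free survival (DFS) is 47.6% for RTA and 32% for TH". It then reports that "we calculated 212 patients (106 in the RTA group and 106 in the TH group) need to be enrolled in this trial". The calculation is attributed to a t-test for two samples, taken one-sided. The error rates and the allowance for loss follow: "The conventional type I error is 5%, the statistical power is 90%, and the dropout rate is 15" per cent. The Intervention section confirms equal allocation. The Statistical analysis section sets significance at a p value of 0.05 or less without saying whether tests are one- or two-sided, and assigns chi-square or Fisher's exact tests to categorical variables. The article gives no standard deviation, hazard ratio, number of events or non-inferiority margin.

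**The concern.** The paragraph gives every input that a two-group superiority calculation needs, so its result can be checked directly. A difference of 15.6 percentage points between rates near 40% is moderate, and about 90 evaluable patients per arm looks far too few to detect it with 90% power.

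This calculation is the only justification given for the size of the trial on its primary outcome. If the power is overstated, the trial runs a much higher risk than declared of missing the difference it was designed to find. The Discussion predicts that RTA will be superior or at least non-inferior, yet no margin is defined. A non-significant result could therefore be taken as support for similarity when it may only reflect low power.

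**Working it through.** **Inputs** (Sample size calculation, except allocation from Intervention): p1 = 0.476, p2 = 0.32, difference 0.156, one-sided α = 0.05 (z = 1.645), power 0.90 (z = 1.282), dropout 15%, allocation 1:1.

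**1. Attempt to reproduce 212.**
- Variance sum: 0.476 × 0.524 + 0.32 × 0.68 = 0.2494 + 0.2176 = 0.4670.
- Unpooled formula: n = (1.645 + 1.282)² × 0.4670 / 0.156² = 8.564 × 0.4670 / 0.02434 = 164.3 per arm. Divided by 0.85, this is 193.3, so 194 per arm and 388 in total.
- Pooled formula: mean rate 0.398, so 2 × 0.398 × 0.602 = 0.4792. Then n = (1.645 × √0.4792 + 1.282 × √0.4670)² / 0.156² = 166.7, so 167 per arm. 167 / 0.85 = 196.5, so 197 per arm and 394 in total.
- Without any dropout allowance the total is still about 330.

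The stated 212 is not reproduced. It is about 54% of the required number (212/394 = 0.538; 212/388 = 0.546).

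**2. Where 106 might come from.** Put 70% power (z = 0.524) into the unpooled formula: 4.706 × 0.4670 / 0.02434 = 90.3 evaluable per arm, and 90.3 / 0.85 = 106.2. That matches the stated 106. The pooled formula at 70% power gives 92.1 and 108.3. The match suggests that the power figure is the wrong element, but does not prove it.

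**3. Power of the planned size.** 106 × 0.85 = 90.1, so about 90 evaluable per arm. In the unpooled calculation the standardised difference is 0.156 / √(0.4670/90) = 2.166. One-sided power is Φ(2.166 − 1.645) = 69.9%; two-sided it is Φ(2.166 − 1.960) = 58.1%.

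| Evaluable per arm | Method | One-sided 5% | Two-sided 5% |
|---|---|---|---|
| 90 | Unpooled | 69.9% | 58.1% |
| 90 | Pooled | 69.1% | 57.2% |
| 90 | t-test on 0/1 outcome (noncentral t, SD 0.48) | 69.6% | 57.7% |
| 106 (no dropout) | Range of the three | 75–76% | 64–65% |

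For the named t-test to reach 90% with 90 per arm, the standard deviation would have to be about 0.36. The stated rates imply √(0.4670/2) = 0.48.

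**4. Difference that 90 per arm can detect.** At one-sided 5% and 90% power, with TH at 32%, RTA would have to reach about 53.1% (unpooled), a difference of about 21 points against the planned 15.6.

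**5. Log-rank reading.** This assumes exponential survival and proportional hazards, which the article does not state. HR = ln 0.476 / ln 0.32 = 0.651, and ln HR = −0.4285. Events needed for 90% power, one-sided: 4 × 8.564 / 0.4285² = 187. The average event probability at 3 years is 1 − 0.398 = 0.602, so 180 evaluable patients yield 180 × 0.602 = 108 events. At 5 years the probability is 0.780, giving 180 × 0.780 = 140 events. Power is Φ(√events / 2 × 0.4285 − 1.645):

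| Reading | Events | One-sided power |
|---|---|---|
| 3 years, 180 patients | 108 | 72% |
| 5 years, 180 patients | 140 | 81% |
| 5 years, 212 patients, no dropout | 165 | 87% |

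None reaches 90%.

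**The case against.** Four points can be made for the plan.

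- **Sidedness.** The sample size paragraph says one-sided, so the 57–58% figure does not follow from its inputs. This is right. The two-sided value applies only if the unspecified 0.05 threshold in the Statistical analysis section is meant as two-sided.
- **Non-inferiority.** The article speaks of superiority or at least non-inferiority, and a margin could explain 212. With all other inputs kept, the unpooled formula with 0.156 + margin in place of 0.156 gives 8.564 × 0.4670 / 0.211² / 0.85 = 106 per arm at a margin of 5.5 points. A margin of about 8 points with one-sided 2.5% also comes close, at about 105. So 70% power is not the only conceivable origin of 106. But the article states no margin, and this would be an undisclosed input, not a reproduction of the figure.
- **Follow-up and censoring.** Patients are followed for at least five years, and dropouts in a time-to-event analysis contribute until they are censored, so removing 15% outright is pessimistic. The most generous version still gives only 87%, and it departs from the 3-year endpoint, the named test and the stated dropout. The section on termination standards also removes terminated patients from the analysis, which works against this argument.
- **Condensed article.** The full protocol may hold more detail. That would excuse an omission, but this paragraph states both its inputs and its result, and they disagree.

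It is also fair to say that nothing in the article commits the investigators to reading a null result as equivalence. That consequence is a risk, not a stated plan.

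**Conclusion.** The concern holds. On the stated superiority inputs, 90% power requires about 388 to 394 enrolled patients. The planned 212 give about 70% power one-sided after the stated dropout, and 75–76% if no one is lost. The chance of missing the planned difference is thus about 30% against the declared 10%, and about 43% if the test is two-sided.

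The result rests on the two rates, the 15% loss and the 1:1 allocation given in the article, and on treating 3-year disease-free survival as a proportion. The choice of formula moves power by about one percentage point. Log-rank readings raise it to between 72% and 87%, depending on follow-up and dropout, and always below 90%. How 212 was actually obtained cannot be settled from the article.

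**What to change.** Correct the Sample size calculation paragraph.

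1. Keep 212 and state the power it gives: about 70% at one-sided 5%, or about 58% at two-sided 5%, for 47.6% against 32% after 15% dropout. Alternatively, state that 212 patients detect about 21 points (about 53% against 32%) with 90% power at one-sided 5%, and say openly that this exceeds the 15.6 points taken from the cited study.
2. Replace the t-test by the test to which the calculation refers: two proportions at 3 years, or log-rank with the required number of events and the follow-up assumed.
3. If 212 came from an input that is not shown, such as a non-inferiority margin or a standard deviation, disclose it with the calculation.
4. If 90% power for the planned difference is to stand, say that the inputs require about 390 patients.

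Restating the figure costs a rewritten paragraph and a less favourable power, with no extra patients. Under Study design, a change that substantially affects the trial goes back to the ethics committee, so the sponsor should decide whether the lower power counts as such a change. Only the fourth option enlarges the trial, by about 176 to 182 patients (388 − 212 and 394 − 212).

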### Statistical analysis

Standard descriptive statistics will be used to analyze the qualitative and quantitative variables, including the relative and absolute frequencies, means, medians, standard deviations, and interquartile ranges. Continuous variables will be compared using Student’s t-tests or Mann−Whitney U tests, while categorical variables will be compared using chi-square tests or Fisher’s exact tests. A confidence of 95% will be considered suitable for analysis. Statistical significance will be defined as a p value of 0.05 or less. IBM SPSS (Version 28, Chicago, USA) will be used to conduct the statistical analysis.

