### Patient follow-up

According to the schedule (**Table 1**), the patients will be followed for the first time one month after surgery and then every three months for three years. An additional follow-up survey of the indicators will be conducted semiannually for the next two years. All patients will be required to be followed for at least five years. Each follow-up will include a physical examination, a routine blood examination and a serum tumor marker examination every three or six months. Enhanced thoracic and abdominal CT will be performed every six months, and gastroscopy will be performed annually. If a tumor recurrence or metastasis is suspected, additional tests will be performed and recorded on the CRF table. Trial-related complications will be assessed based on the Clavien−Dindo classification. If grade III or above complications occur, they will be reported to the responsible unit of the project, fed back to the study supervision department, and comprehensively evaluated to how to deal with this situation in time and effectively. All follow-up will be performed by the project’s professional follow-up team. The trial will be completed until the last patient completes their follow-up.

**Table 1 T1:** Checklist for collection of necessary clinical data and follow-up schedule of enrolled patients.

	Baseline information				Follow-up (months)																
	Preoperation	Operation	POD 1-7	Discharge	1	3	6	9	12	15	18	21	24	27	30	33	36	42	48	54	60
Demography	√																				
Informed consent	√																				
Medical history	√																				
Oncological history	√																				
Tumor classification	√																				
Biometric data	√																				
Laboratory	√						√		√		√		√		√		√	√	√	√	√
Physical examination	√				√	√	√	√	√	√	√	√	√	√	√	√	√	√	√	√	√
Inclusion / Exclusion	√																				
Randomisation	√																				
Anamnesis	√				√	√	√	√	√	√	√	√	√	√	√	√	√	√	√	√	√
Gastroscopy	√								√				√				√		√		√
Enhanced thoracic and abdominal CT	√						√		√		√		√		√		√	√	√	√	√
Abdominal ultrasound	√						√		√		√		√		√		√	√	√	√	√
Concomitant Medication	√			√	√	√	√	√	√	√	√	√	√	√	√	√	√	√	√	√	√
Surgical information		√																			
Pathology				√																	
postoperative complications			√	√	√																
postoperative mortality			√	√	√																
local recurrence rate				√	√	√	√	√	√	√	√	√	√	√	√	√	√	√	√	√	√
surgical Apgar score		√																			
SF-36	√			√	√	√	√	√	√	√	√	√	√	√	√	√	√	√	√	√	√

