EORTC QLQ-C30	√			√	√	√	√	√	√	√	√	√	√	√	√	√	√	√	√	√	√
EORTC QLQ-OES18	√			√	√	√	√	√	√	√	√	√	√	√	√	√	√	√	√	√	√
**Disease-free survival**					√	√	√	√	√	√	√	√	√	√	√	√	√	√	√	√	√
Overall survival					√	√	√	√	√	√	√	√	√	√	√	√	√	√	√	√	√

√, Indicates the need to collect the clinical data

SF-36, Short-Form 36; EORTC QLQ-C30, European Organization for Research and Treatment of Cancer Quality of Life Questionnaire Core 30; EORTC QLQ-OES18, Computerized adaptive test European Organization for Research and Treatment of Cancer Quality of Life Questionnaire for Esophageal cancer.

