### Outcome measures

The primary outcome is a comparison of 3-year disease-free survival (DFS) between the two groups. The secondary outcomes of the trial included 5-year overall survival (OS), incidence of postoperative complications, postoperative mortality, local recurrence rate, the number of lymph nodes, quality of life (QOL) score, surgical Apgar score and duration of the operation. All types of postoperative complications will be defined by the Esophageal Complications Consensus Group (ECCG) (22) and classified by the Clavien−Dindo grading system (23). A variety of questionnaires will be used to assess QOL. General health aspects will be measured by the SF-36 and CAT EORTC QLQC30, whereas esophageal health will be assessed by the CAT EORTC QLQ-OES18 (24).

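### Quality of life is measured before surgery on all three instruments, but the only comparison stated for continuous variables is unadjusted, which costs precision (not validity) on a secondary outcome

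*Protocol article*

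**What the plan says.** The Outcome measures section of the protocol article lists the quality-of-life (QOL) score among the secondary outcomes and names the instruments: "General health aspects will be measured by the SF-36 and CAT EORTC QLQC30, whereas esophageal health will be assessed by the CAT EORTC QLQ-OES18".

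Table 1 in Patient follow-up ("Checklist for collection of necessary clinical data and follow-up schedule of enrolled patients") ticks all three instruments in the preoperative column, at discharge, and at each of the 17 follow-up visits from month 1 to month 60. Every patient is therefore scheduled to have a baseline value of the outcome itself and up to 18 later values.

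The Statistical analysis section gives the method in general terms: "Continuous variables will be compared using Student’s t-tests or Mann−Whitney U tests", with chi-square or Fisher tests for categorical variables. It adds "Statistical significance will be defined as a p value of 0.05 or less" and names SPSS version 28. Nowhere does the article mention a baseline covariate, a change score or a longitudinal model for QOL.

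The sample size rests on disease-free survival (DFS) alone: "we calculated 212 patients (106 in the RTA group and 106 in the TH group) need to be enrolled". No effect size, correlation or power is given for QOL.

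**The concern.** When an outcome is measured before treatment, its baseline value is usually one of the strongest available predictors of later values. A two-sample test on follow-up scores leaves the variation explained by baseline in the error term, so the interval for the arm difference is wider than the collected data allow. A two-sample test on change from baseline removes some of that variation but adds the noise of the baseline measurement. At low correlation the second effect is larger than the first.

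The trial is not sized for QOL, so precision there depends on how well the scheduled data are used. The Abstract and Discussion both expect the right thoracoabdominal approach to come with a high quality of life, so readers will look at this result. The article does not merely leave the method open: it names the tests for continuous variables, and an analyst who followed it as written would not adjust.

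**Working it through.** **Plan's own figure.** There is none for QOL. The stated 212 patients relate to DFS and are used here only to obtain a number per arm; whether 212 follows from its own inputs is a separate question.

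**Inputs from the protocol article**
- 106 per arm and 15% dropout (Sample size calculation): 106 × 0.85 = 90.1, taken as 90 per arm.
- Significance level 0.05 (Statistical analysis).

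**Assumptions, not in the documents**
- Correlation ρ between the preoperative and follow-up score: 0.3 to 0.7.
- Illustrative arm difference d = 0.4 SD, and a two-sided test.
- 90 per arm with a score at the visit analysed.
- Equal variances at the two time points and a linear relation between the scores.

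**Variance of the arm difference at one visit, relative to a t-test on follow-up scores**
- t-test on follow-up scores: 1
- t-test on change scores: 2(1 − ρ)
- ANCOVA on the preoperative score: 1 − ρ²

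Since 1 − ρ² = (1 − ρ)(1 + ρ), ANCOVA has the smaller variance than change scores for every ρ below 1. The change-score test is worse than the plain t-test when 2(1 − ρ) exceeds 1, that is, when ρ is below 0.5.

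**Power** = Φ( d / √(2V/n) − 1.96 ), where V is the relative variance.

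Unadjusted: √(2/90) = 0.1491; 0.4/0.1491 = 2.683; 2.683 − 1.96 = 0.723; Φ(0.723) = 76.5%.

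ANCOVA at ρ = 0.5: 2.683/√0.75 = 3.098; 3.098 − 1.96 = 1.138; Φ(1.138) = 87.3%.

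**Detectable difference** at 80% power = (1.96 + 0.842) × 0.1491 × √V. Unadjusted, this is 0.418 SD.

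| ρ | Change-score variance | ANCOVA variance | Variance cut by ANCOVA | ANCOVA power at 0.4 SD | Gain over 76.5% (points) | Detectable difference, ANCOVA (SD) |
|---|---|---|---|---|---|---|
| 0.3 | 1.40 | 0.91 | 9% | 80.3% | 3.8 | 0.398 |
| 0.4 | 1.20 | 0.84 | 16% | 83.3% | 6.8 | 0.383 |
| 0.5 | 1.00 | 0.75 | 25% | 87.3% | 10.8 | 0.362 |
| 0.6 | 0.80 | 0.64 | 36% | 91.8% | 15.3 | 0.334 |
| 0.7 | 0.60 | 0.51 | 49% | 96.4% | 19.9 | 0.298 |

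In terms of patients, ANCOVA at ρ = 0.5 needs 90 × 0.75 = 67.5, about 68 per arm, to match the unadjusted test with 90. Confidence intervals are 1 − √0.75 = 13% narrower.

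**Where the gain is small.** With 90 per arm and d = 0.4, the gain is 1.7 points at ρ = 0.2 and 0.4 points at ρ = 0.1. At ρ = 0.5 it is 5.4 points for d = 0.5. For d = 0.6 it is only 1.6 points, because unadjusted power is already 98%.

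**The case against.** The strongest reply is that the Statistical analysis section is a short generic paragraph in a journal article. It does not mention QOL, and it names no survival method even for the primary outcome, so it can hardly be an exhaustive list. The model for one secondary questionnaire outcome is the kind of detail a separate analysis plan would settle. This stands in part: the paragraph does not say which QOL quantity is tested, and an analysis plan that is not shown may adjust. But the article does state a method for continuous variables, QOL scores fall within it as written, and a better method is available from the same data.

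Three stronger readings are tempting, and the documents do not support them.

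- **That the baseline score is discarded.** This follows only if follow-up scores are tested. A t-test or Mann-Whitney test on change scores fits the wording equally well and does use the baseline, though less efficiently than ANCOVA.
- **That the comparison is biased, or left open to chance baseline imbalance.** With randomisation, the type I error of the unadjusted test already allows for chance imbalance.
- **That the planning DFS rates (47.6% and 32% at 3 years) imply heavy or unequal loss of questionnaires.** A DFS event includes recurrence in a living patient. Patient follow-up requires at least five years for everyone, and Table 1 continues the questionnaires to month 60 with no stop at recurrence. No form-return rate is given. Nor would a mixed model by itself deal with death or with missingness that depends on unobserved scores.

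It also stands that the effect size and correlation are assumed, and that the documents state no between-arm QOL difference that the trial is meant to detect.

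**Conclusion.** The point holds as a matter of efficiency. The stated tests are valid but less precise than the scheduled data allow, whether they are run on follow-up scores or on change scores.

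For correlations of 0.3 to 0.7, baseline adjustment reduces the variance of the arm difference by 9% to 49%. At 0.4 SD with 90 per arm, it raises power from about 76% to between 80% and 96%. These sizes rest on the assumed correlation, effect size and number evaluable; the direction holds for any non-zero correlation, apart from a negligible loss of degrees of freedom. At correlations below 0.3, or where the unadjusted test already has high power, the gain is only a point or two.

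The outcome is secondary and the primary analysis is untouched, so this is a free improvement rather than an error that threatens the trial's conclusions.

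**What to change.** Add to the Statistical analysis section that each QOL score will be compared between arms with its preoperative value as a covariate, in one of two ways:

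- ANCOVA at one prespecified visit; or
- a mixed model for repeated measures with baseline score, arm, visit and arm-by-visit interaction, reporting the arm difference and 95% confidence interval at that prespecified visit.

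The t-test and Mann-Whitney test can remain for continuous outcomes with no baseline value, such as duration of the operation.

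The cost is a sentence or two of analysis text. The preoperative and follow-up questionnaires are already scheduled, no patients or visits are added, and the SPSS software already named fits both models. The visit should be chosen, and the wording fixed, before any QOL data are compared by arm.

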### Ethical approval and consent to participate

This is a prospective multicenter randomized controlled study aiming to identify the optimal surgical approach for Siewert II AEG. All legal requirements, regulations, and general principles of conduct in human biomedical research will be strictly followed in this study. In addition, the Declaration of Helsinki and the International Code of Ethics for Biomedical Research Involving Humans are essential principles guiding the conduct of this research. Clinical trials registered with the Chinese Ethics Committee have approved the research (Approval No. ChiECRCT20210635, 30 January 2022). The ethics committee is obliged to assess the progress of the research periodically and will be notified in case of any adverse events (AES).

## Discussion

The incidence of adenocarcinoma at the esophagogastric junction (AEG) has increased from 22.3% to 35.7% in the last few decades (4). AEG is highly likely to recur and metastasize, which results in a poor outcome (27). Surgical resection is considered to be the main curative treatment with a favorable prognosis. As the minimally invasive techniques of laparoscopy and thoracoscopy are in widespread use, the choice of surgical methods has become more diverse. Lymph nodes may be dissected by various surgical approaches, which will have a strong impact on the prognosis. However, intense debate has raged for decades regarding the proper operative approach for AEG, especially for Siewert II AEG (8).

The previous literature has shown that the main surgical methods for Siewert II AEG include TH and TA (7). A 10-year follow-up of the JCOG9502 study in Japan showed that LTA was not only ineffective in improving overall or disease-free survival but also increased postoperative morbidity. Therefore, in cases of esophageal invasion depths under 3 cm in AEG type II tumors, they recommended avoiding the LTA approach. However, that study had some limitations, such as a failure to show survival differences between the two procedures, not including minimally invasive procedures, and using only LTA instead of the Ivor-Lewis approach (28).

In recent years, a large number of studies have shown that the LTA approach is inferior to the RTA in terms of the number of lymph nodes dissected, long-term survival, recurrence and prognosis, causing the LTA approach to fall out of favor (6, 14, 15, 29). Compared with the LTA approach, Blank et al. found that the RTA (Ivor-Lewis operation) had a significantly longer survival time than the TH approach. Multivariate analysis showed that the surgical type was an independent prognostic factor. Nevertheless, that study was a single-center, nonrandomized, controlled study that did not use minimally invasive surgery (10). In contrast, a single-center retrospective study found that the TH is more effective in achieving an optimal extent of lymph node dissection, reducing complications, shortening hospital stays, and promoting recovery (11). Although RTA has great advantages in mediastinal lymph node dissection, ensuring a negative esophagectomy margin and completing gastrointestinal reconstruction, it also invades the chest and increases the incidence of chest-related complications (10, 12).

With the introduction of laparoscopic fundoplication in 1991, minimally invasive surgical approaches have been noticed and accepted by a wide range of surgeons and have the potential to reduce surgical morbidity, especially pulmonary complications, promote postoperative recovery and improve the postoperative survival rate, along with leaving only small incisions (25, 30, 31). Therefore, a minimally invasive approach may greatly improve the defects of the TA approach by eliminating its higher postoperative complications. Li KK et al. found that compared with single laparoscopic surgery, a multiple thoracoscopic operation produced little additional trauma to patients and did not increase the incidence of postoperative complications or mortality (32). However, as most of these results are retrospective studies and small in size, their conclusions should be treated with caution.

Currently, no prospective randomized controlled trials have been conducted of minimally invasive surgery for Siewert II AEG. This study will be the first multicenter randomized controlled trial focusing on Siewert II AEG treated with minimally invasive surgery, comparing the clinical efficacy of RTA versus TH. Upon successful completion of this study, we will be able to provide basic information associated with each surgical approach about disease-free survival, overall survival, postoperative complications, tumor outcomes and prognosis. The objective of this trial is to determine whether the RTA approach for Siewert II AEG patients is superior to or at least noninferior to TH in terms of surgical safety. In conclusion, the results of this study will provide clinical guidelines for choosing an approach for Siewert II AEG surgery. We hypothesized that the efficacy of digestion tract reconstruction and dissection of mediastinal lymph nodes by RTA would be better. We predict that when using minimally invasive techniques, the 3-year disease-free survival, 5-year overall survival and other prognostic indicators of RTA will be superior to or at least noninferior to that of TH, while providing a high quality of life and good postoperative outcome.

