## Abstract

**Background:**

Siewert type II adenocarcinoma of the esophagogastric junction (Siewert II AEG) can be resected by the right thoracoabdominal surgical approach (RTA) or abdominal-transhiatal surgical approach (TH) under minimally invasive conditions. Although both surgical methods achieve complete tumor resection, there is a debate as to whether the former method is superior to or at least noninferior to the latter in terms of surgical safety. Currently, a small number of retrospective studies have compared the two surgical approaches, with inconclusive results. As such, a prospective multicenter randomized controlled trial is necessary to validate the value of RTA (Ivor-Lewis) compared to TH.

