## Methods

### Objective

The purpose of this trial is to compare RTA with TH for resectable Siewert II AEGs based on surgical safety, clinical efficacy and prognosis. The primary outcome of the study will be the 3-year disease-free survival (DFS) to assess the oncological safety of the procedure. The secondary outcomes will be 5-year overall survival (OS), incidence of postoperative complications, postoperative mortality, local recurrence rate, number and location of removed lymph nodes, surgical Apgar score, duration of the operation and the quality of life (QOL) score.

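### The Discussion states a noninferiority aim in surgical safety (and predicts it for DFS and OS), but the printed design is sized and tested only for a difference, on DFS, with no margin

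*Protocol article*

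**What the plan says.** The Discussion states the objective as determining "whether the RTA approach for Siewert II AEG patients is superior to or at least noninferior to TH in terms of surgical safety". It then predicts that 3-year DFS, 5-year OS and "other prognostic indicators of RTA will be superior to or at least noninferior to that of TH". The Abstract's Background paragraph uses similar words, but to describe an open debate: "whether the former method is superior to or at least noninferior to the latter in terms of surgical safety".

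The Methods define a different trial:
- **Objective:** "The primary outcome of the study will be the 3-year disease-free survival (DFS) to assess the oncological safety of the procedure". Postoperative complications, postoperative mortality and the surgical Apgar score are secondary. Outcome measures repeats this ranking.
- **Sample size calculation:** the inputs are that "the 3-year disease-free survival (DFS) is 47.6% for RTA and 32% for TH", and the size was obtained "using a one-sided two-sample t-test", with 5% type I error, 90% power and 15% dropout, giving 212 patients (106 per arm).
- **Statistical analysis:** t-tests, Mann–Whitney, chi-square and Fisher's exact tests, with significance at p of 0.05 or less.

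No margin is given for any endpoint.

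**The concern.** The stated objective differs from the sized trial in two ways. The hypothesis differs: noninferiority needs a prespecified margin and a confidence bound compared with it, while the plan provides for detecting a difference. The endpoint differs too: surgical safety is not 3-year DFS. The Objective itself lists surgical safety separately from clinical efficacy and prognosis, and ties DFS to oncological safety.

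The article cites evidence of more cardiovascular, respiratory and chest-related complications with RTA, and says that the results will inform clinical guidelines. A claim of noninferior surgical safety would therefore bear on the main risk that the article itself raises against RTA. It should not rest on a design that was not built to test it.

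**Working it through.** **Inputs.** From Sample size calculation: 3-year DFS 47.6% (RTA) and 32% (TH), difference 15.6 points, midpoint (47.6 + 32)/2 = 39.8%; one-sided 5%, 90% power, 15% dropout, 106 per arm. Evaluable per arm: 106 × 0.85 = 90.1, taken as 90. My assumptions: equal true DFS for the noninferiority calculation, one-sided 5% or 2.5% for the noninferiority bound, and 80% power as an alternative.

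**1. The plan's own figure.** For superiority with a pooled two-proportion test, per arm:

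n = [1.645 × √(2 × 0.398 × 0.602) + 1.282 × √(0.476 × 0.524 + 0.32 × 0.68)]² / 0.156² ≈ 167.

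That is 334 in total. With dropout, 167/0.85 gives 197 per arm, or 394. With a continuity correction it is 180 per arm, which becomes 212 per arm (424 in total) after dropout. The stated 212 in total is not reproduced. This is a separate problem. Its relevance here is that the inputs contain a superiority difference and nothing that could serve as a margin.

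**2. Smallest DFS margin that this size supports.** With equal true DFS p and n per arm:

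margin = (z for alpha + z for power) × √(2p(1 − p)/n).

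Example with p = 0.398, n = 90: √(2 × 0.398 × 0.602/90) = 0.0730. At one-sided 5% and 90% power, (1.645 + 1.282) × 0.0730 = 21.4 points. At one-sided 2.5%, (1.960 + 1.282) × 0.0730 = 23.7 points.

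| 90 per arm | p = 32% | p = 39.8% | p = 47.6% |
|---|---|---|---|
| one-sided 5%, 90% power | 20.3 | 21.4 | 21.8 |
| one-sided 2.5%, 90% power | 22.5 | 23.7 | 24.1 |
| one-sided 5%, 80% power | 17.3 | 18.1 | 18.5 |
| one-sided 2.5%, 80% power | 19.5 | 20.4 | 20.9 |

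Every entry exceeds the 15.6-point benefit on which the trial is sized. With all 106 per arm evaluable, the 90%-power range is 18.8 to 22.2 points.

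**3. The same calculation under the plan's assumed benefit.** SE = √((0.476 × 0.524 + 0.32 × 0.68)/90) = 0.0720. The margin needed is 2.926 × 0.0720 − 0.156 = 5.5 points (one-sided 5%) or 3.242 × 0.0720 − 0.156 = 7.8 points (one-sided 2.5%). A small margin is within reach only if RTA really has the large advantage.

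**4. What non-significance would show.** Suppose RTA is truly 10 points worse, 29.8% against 39.8%. With 90 per arm, SE = √((0.298 × 0.702 + 0.398 × 0.602)/90) = 0.0706 and 0.10/0.0706 = 1.416. The chance of significance in a two-sided 5% test is Φ(1.416 − 1.960) = 0.29, so the result is non-significant 71% of the time. With 106 per arm, SE = 0.0651, the ratio is 1.537, and the result is non-significant 66% of the time. A one-sided test in favour of RTA is not built to flag harm at all.

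**5. Safety.** The document gives no expected complication or mortality rate, so no safety margin can be computed from it.

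**The case against.** The best defence is that the Methods are coherent on this point. Objective and Outcome measures speak of comparing the approaches with 3-year DFS as the primary outcome, and neither mentions noninferiority. The aim rests on two sentences in the Discussion, and the Abstract's Background only describes a debate. All of this is right, and it limits the seriousness. But one of those two sentences is worded as the objective of the trial, so it cannot be set aside as loose commentary.

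It can also be said that a margin belongs in an SAP or full protocol that is not shown. An SAP could add a margin, but it could not make a sample size fit a hypothesis for which it was not calculated, and the article prints the basis of its sizing.

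The 20-to-24-point figure is open to challenge as well. It is conditional: DFS only, equal true rates, 90% power. Step 3 shows that it falls to 5.5 to 7.8 points under the plan's own rates. That stands, so the figure is an illustration, not a property of the design. In that scenario, though, superiority would be the natural claim.

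A reader might infer more than the text supports:
- That the trial promises to show noninferiority. The text speaks of determining whether (safety) and of a prediction (DFS and OS).
- That a non-significant result will be reported as noninferiority, so that almost any outcome counts as success. No section says so. The article merely describes no valid route to that conclusion.
- That the 20-to-24-point range also applies to surgical safety. With no event rates given, it cannot be carried over.

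**Conclusion.** The point holds as an inconsistency between the stated objective and the printed design. The Discussion names a noninferiority alternative for surgical safety and predicts it for DFS and OS. The Methods size and test only a difference, with DFS as primary, no margin for any endpoint and no powered safety endpoint. The design as printed therefore cannot deliver a noninferiority conclusion.

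For scale, on DFS only: about 20 to 22 points (one-sided 5%) or 22.5 to 24 points (one-sided 2.5%) is the smallest margin supportable at 90% power, and about 17 to 21 points at 80% power, assuming equal true DFS of 32 to 47.6% and 90 evaluable per arm.

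This should be corrected, but it is a matter of wording: the primary endpoint, allocation and data collection are unaffected.

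**What to change.** 1. State one confirmatory hypothesis: superiority of RTA over TH on 3-year DFS.
2. In the Discussion, remove the noninferiority alternative from both the objective and the prediction.
3. Align the surgical-safety framing in the Abstract (Background and Discussion paragraphs) and in Objective with the DFS primary outcome. The Abstract's Background may still describe the debate, but should not read as the trial's aim.
4. State that a non-significant result will not be interpreted as noninferiority.
5. Report complications, mortality and the surgical Apgar score as secondary estimates with 95% confidence intervals, without a noninferiority verdict.

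The cost is wording only; the sponsor gives up a claim that the design cannot support. Keeping the claim would need a justified margin and a new sample size. Purely as an illustration, a 10-point DFS margin at 32% in both arms and 90% power needs 2.926² × 2 × 0.32 × 0.68/0.10² ≈ 373 per arm at one-sided 5%, or 878 in total after 15% dropout (458 per arm and 1,078 in total at one-sided 2.5%).

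This fix does not resolve the separate problem that 212 does not follow from the stated inputs. The superiority test to be relied on has about 69 to 75% power at one-sided 5% (90 and 106 per arm), not 90%.
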